**Figure 2 fig2:**
[figure not shown]
Acupoint locations for ACE of mild psoriasis combined with overweight.

The “cun” is a relative unit of measurement in acupuncture, individually defined for each participant. One cun is equivalent to the width of the participant’s interphalangeal joint of the thumb.

(2) Control group:

To ensure rigorous blinding and control for the placebo effect, participants in the control group will receive a sham ACE procedure. This procedure is designed to be indistinguishable from the verum ACE in terms of visual, tactile, and procedural experience: A third-party researcher provided the acupuncturist with a pre-packed kit containing 14 disposable embedding needles corresponding to the patient’s randomization number. The acupuncturist, who remained blinded to the group assignment, performed the procedure directly using the provided kit. Although the sham procedure mimics the motions of needle insertion, thread embedding, and needle withdrawal, no absorbable suture is actually embedded.

### The procedure of acupuncture thread embedding

2.13

To maintain allocation concealment, a third-party researcher not involved in the clinical assessment will prepare the needles according to the randomization schedule all procedures will be performed in accordance with the “Acupuncture Technical Operation Standards, Part 10: Acupoint Embedding (43).” The intervention will be conducted in a temperature-controlled room under strict aseptic conditions.

Practitioners will adhere to standard surgical hand-hygiene protocols and wear sterile cap and mask. For the verum group, opaque, disposable ACE needles (0.7 × 60 mm; Su Food and Drug Administration Medical Device Manufacturing License 20010244) will be preloaded with a 2 cm segment of absorbable surgical suture (Zhejiang Food and Drug Administration Medical Device Manufacturing License 20110110). See Figure 3.

**Figure 3 fig3:**
[figure not shown]
ACE needle and absorbed sutures.

For the verum group, the needle will be inserted manually into the selected acupoints. The ST25, SP15, CV12 and ST36 will be punctured perpendicularly, with an insertion depth of approximately 25–35 mm. The BL18 and BL20 will be punctured at a 45°angle to the skin, with an insertion depth of about 15–20 mm. Once the acupoint sensation is achieved, the practitioner withdraws the needle while pushing the absorbable thread into the muscle layer using the needle core. Immediately following, needle withdrawal, the puncture sites will be promptly compressed with sterile dry cotton swabs to prevent bleeding. The placement of the thread depends on the depth of the needling, and the practitioner will not feel any resistance while inserting the absorbable thread. The treatment will be administered once every 2 weeks for a total of four sessions, lasting 8 weeks (24, 34).

For the sham group: using the same disposable needles (with the catgut suture pre-removed), the practitioner performed an identical procedure—insertion into the muscle layer followed by a simulated “pushing-withdrawing” action—ensuring the same tactile experience for participants as the verum group, with the sole difference being the absence of actual suture embedding.

A sham procedure was selected as the control for​ the following reasons: (1) to ensure rigorous trial design: as a double-blind, randomized controlled trial, a sham procedure is essential. It matches the verum ACE in every visible aspect, ensuring effective participant blinding and controlling for non-specific effects (e.g., placebo, natural disease variation). This allows for an objective evaluation of the specific therapeutic effect attributable to the catgut embedding itself. (2) to demonstrate specific efficacy beyond standard care limitations: Current standard treatments for mild psoriasis have limitations, including side effects and lack of efficacy for obesity. This trial aims to prove that ACE offers a specific therapeutic benefit, which necessitates comparison against a non-active intervention to establish its distinct clinical value.

Participation will be discontinued if any of the following criteria are met: (1) failure to attend scheduled outpatient follow-ups on time; (2) occurrence of serious adverse reactions; (3) changes in the participant’s medical condition that render continued participation inappropriate; (4) the participant or their legal guardian requests to stop.

### Participant management and safety

2.14

Participants are encouraged to maintain open communication with the research team, and all inquiries will be addressed promptly throughout the study. To facilitate adherence to the visit schedule, transportation reimbursements will be provided for all study-related appointments. Following the intervention period, all participants will remain under routine clinical observation by the research team. Participants will be instructed to promptly report any discomfort or potential adverse reactions to the coordinator. Upon such notification, the research team will evaluate the condition and arrange appropriate post-trial care, including specialist consultations at no cost to the participant. All adverse events will be managed in accordance with standard clinical protocols, and all trial-related medical expenses will be fully covered by the study.

### Data collection procedures

2.15

The study comprises an 8 weeks intervention period followed by a 32-week follow-up phase. During the intervention, data collection and clinical assessments will occur biweekly. Post-intervention follow-up evaluations are scheduled every four weeks through week 24, with a final assessment at week 32.

To explore the biological underpinnings of the therapeutic response, peripheral venous blood samples will be collected at baseline (week 0), mid-intervention (week 4), end-of-treatment (week 8), and at the final follow-up (week 32). These supplementary samples will support exploratory multi-omics analyses, including single-cell sequencing, untargeted metabolomics, and proteomics (Figure 4). A comprehensive schedule of all assessment items is provided in Table 1.

**Figure 4 fig4:**
[figure not shown]
Data node collection diagram.

**Table 1 tab1:** The complete set of assessment items.

Project	0 W	4 W	8 W	12 W	16 W	24 W	32 W
PASI	**×**	**×**	**×**	**×**	**×**	**×**	**×**
BSA	**×**	**×**	**×**	**×**	**×**	**×**	**×**
PGA	**×**	**×**	**×**	**×**	**×**	**×**	**×**
Itch NRS score	**×**	**×**	**×**	**×**	**×**	**×**	**×**
DLQI	**×**	**×**	**×**	**×**	**×**	**×**	**×**
BMI	**×**	**×**	**×**	**×**	**×**	**×**	**×**
WC	**×**	**×**	**×**	**×**	**×**	**×**	**×**
WHR	**×**	**×**	**×**	**×**	**×**	**×**	**×**
Blood pressure	**×**	**×**	**×**	**×**	**×**	**×**	**×**
Traditional Chinese Medicine Syndrome Scoring	**×**	**×**	**×**				
ESR, CRP	**×**	**×**	**×**				**×**
Lipid profile	**×**	**×**	**×**				**×**
Blood glucose	**×**	**×**	**×**				**×**
Blood uric acid	**×**	**×**	**×**				**×**
Peripheral blood sample	**×**	**×**	**×**				**×**

If female, additional baseline blood HCG tests are required.

We will assess the safety of acupoint embedding therapy through the collection of biological sample information, including but not limited to general data, blood pressure, heart rate, and blood sample collection (Table 2).

**Table 2 tab2:** Safety indicators.

Project	0 W	4 W	8 W	12 W	16 W	24 W	32 W
Basic information	**×**						
Medical information	**×**						
Complete blood count	**×**		**×**				
Liver function, kidney function	**×**		**×**				
Electrocardiogram (ECG)	**×**		**×**				
AEs		**×**	**×**	**×**	**×**	**×**	**×**

### Participant timeline

2.16

The schedule of enrollment, interventions, and assessments is summarized in Figure 5.

**Figure 5 fig5:**
[figure not shown]
Participant timeline.

### Plans for assessment and collection of outcome

2.17

To reduce costs, all research institutes will undergo unified training, including tasks such as data collection and data calculation. All experiments will be conducted by a single operator.

1 Measurement of psoriasis-related outcome indicators

PASI, BSA, PGA, DLQI, and itch VAS score are widely used outcome measures in psoriasis research (44–47). Their measurement methods are as follows:

(1) *PASI* (48): the PASI score will be assessed using the standard PASI scoring system. Two independent, uniformly trained investigators will perform the evaluations separately, and the average score will be calculated.(2) *BSA*: BSA involvement will be evaluated by two independent, uniformly trained investigators. The palmar surface of one hand (including fingers) will be considered as 1% of the total BSA. The investigators will assess the affected area separately, and the average value will be recorded.(3) *PGA*: the PGA will be performed by physicians, who will comprehensively evaluate the participants’ psoriatic lesions based on erythema, scaling, and infiltration (thickness). The assessment will utilize a 0–4 point scale, with lower scores indicating milder disease severity.(4) *DLQI* (49): the DLQI will be assessed using the standard DLQI questionnaire. Study participants will complete the questionnaire under investigator guidance to evaluate the impact of psoriasis on their quality of life.(5) *Itch VAS score (VAS)*: the VAS will be used to assess participants’ subjective itching sensation. Participants will rate their itch intensity on the VAS scale.2 Body weight and metabolism-related indicators and assessment methods

After the expert panel discussed within our research team, the following parameters will be included in the assessment: BMI, WC, hip circumference, WHR, blood pressure, blood lipids, and blood glucose (50–53). The measurement methods are as follows:

(1) *BMI* (54): BMI will be calculated as weight (kg) divided by height squared (m^2^), following measurement of participants’ height and weight. BMI categories (kg/m^2^) are defined as: underweight (< 18.5), normal (18.5–23.9), overweight (24–27.9), and obesity (≥ 28).(2) *WC*: WC will be measured using a non-elastic tape. Participants will stand upright with feet 25–30 cm apart, weight evenly distributed, shoulders and abdomen relaxed, and breathing normally. The measurement will be taken at the midpoint between the lower margin of the last palpable rib and the top of the iliac crest (approximately 0.5–1.0 cm above the umbilicus), with the tape horizontal and snug but not compressing the skin. A WC of ≥ 80 cm in women and ≥ 85 cm in men will indicate possible abdominal obesity, while a WC of ≥ 85 cm in women and ≥ 90 cm in men will indicate central obesity.(3) *Hip circumference (HC)*: HC will be measured using a non-elastic tape. Participants will stand upright with feet together, arms at their sides, and breathing normally. The measurement will be taken at the point of greatest gluteal protrusion.(4) *WHR*: WHR will be calculated as WC divided by HC. Normal values are defined as ≤ 0.85 for men and ≤ 0.80 for women.(5) *Blood pressure*: blood pressure will be measured by trained medical personnel using a sphygmomanometer. The average reading from both arms will be recorded. Hypertension associated with obesity is defined as ≥ 140/90 mmHg. The types and doses of antihypertensive medications used by participants will be documented.(6) *Lipid profile*: laboratory analyses, including triglycerides (TG), low-density lipoprotein cholesterol (LDL-C), high-density lipoprotein cholesterol (HDL-C), and total cholesterol (TC), will be ordered by physicians and performed by the hospital laboratory. The types and doses of lipid-lowering medications used by participants will be recorded.(7) *Blood glucose*: laboratory analyses, including fasting blood glucose (FBG), glycated hemoglobin (HbA1c), and serum insulin, will be ordered by physicians and performed by the hospital laboratory. The types and doses of glucose-lowering medications used by participants will be recorded.(8) *Serum uric acid*: serum uric acid levels will be measured by the hospital laboratory. The types and doses of uric acid-lowering medications used by participants will be recorded.

3 Safety indicators and assessment methods

Complete blood count, liver function, and renal function: laboratory tests including complete blood count, liver function, and renal function were ordered by physicians and performed by the hospital laboratory.

(1) *ECG*: ECG was ordered by physicians and performed by the hospital ECG department.(2) *AEs*: AEs were reported by study participants during the intervention and follow-up periods, regardless of their relationship to the study intervention.

All data collection time points are shown in Tables 1, 2.

### Retention strategies

2.18

In order to keep the participants involved for as long as possible, we implemented a comprehensive approach which included among others: a logistical support (transportation subsidies, flexible scheduling, and reminders via SMS/phone/WeChat), active engagement (regular health education, a dedicated app for calorie tracking, and personal progress feedback), and a system of rewards (compensation for time and travel at every visit). For those who dropped out, an early termination visit was organized to obtain primary/secondary efficacy outcomes (with consent), safety data, reasons for withdrawal, and final medication records. Data from lost to follow-up participants who had done at least two assessments were considered and counted in the intention-to-treat (ITT) analysis.

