### Withdrawal criteria

2.8

Participation will be discontinued if any of the following criteria are met:

(1) Failure to attend scheduled outpatient follow-ups on time.(2) Occurrence of serious adverse reactions.(3) Changes in the participant’s medical condition that render continued participation inappropriate.(4) The participant or their legal guardian requests to stop.

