#### Data handling for terminated cases

2.8.1

For participants who are withdrawn, all collected data will be retained in the case report forms. The last available observation will be used as the final outcome for both efficacy and safety analyses.

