### Statistical methods

2.21

All participants who provided written informed consent and completed baseline assessments will be included in the primary analysis, consistent with the ITT principle. Data will be analyzed according to the group to which participants will be initially randomized, regardless of treatment adherence, protocol deviations, or loss to follow-up, to minimize selection bias and reflect real-world clinical effectiveness. For missing data, a stratified strategy will be adopted: preference will be given to filling in missing values using existing data through multiple imputation or mixed-effects models, while also conducting per-protocol set analyses (including only participants with ≥ 80% compliance) as sensitivity verification; for categorical data, if the proportion of missing values is ≤ 5%, the indicator will be directly excluded, and if it is > 5%, the FIML method will be used.

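### Two sections define the ITT set in conflicting ways, and discontinuation for late attendance is not separated from outcome collection, so week-8 PASI and BMI may go unobserved

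*Protocol article*

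**What the plan says.** **Analysis set.** Section 2.21 (Statistical methods) opens with: "All participants who provided written informed consent and completed baseline assessments will be included in the primary analysis, consistent with the ITT principle". The next sentence assigns participants to the group to which they were randomised, "regardless of treatment adherence, protocol deviations, or loss to follow-up, to minimize selection bias". Section 2.18 (Retention strategies) sets a further condition for those lost: "Data from lost to follow-up participants who had done at least two assessments were considered and counted in the intention-to-treat (ITT) analysis".

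**Discontinuation.** Section 2.8 (Withdrawal criteria) lists as its first reason: "Failure to attend scheduled outpatient follow-ups on time". The end of section 2.13, after Figure 3, repeats it: "Participation will be discontinued if any of the following criteria are met: (1) failure to attend scheduled outpatient follow-ups on time". Neither place distinguishes stopping the procedure from stopping measurement.

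**Data after discontinuation.** Section 2.8.1 keeps withdrawn participants' data and adds: "The last available observation will be used as the final outcome for both efficacy and safety analyses". Section 2.18 provides an early termination visit, with consent, at which primary and secondary efficacy outcomes are sought. It does not tie that visit to week 8. In section 2.21, "preference will be given to filling in missing values using existing data through multiple imputation or mixed-effects models", while the last sentence of the same section calls for complete cases with no imputation.

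**Primary analysis.** Sections 2.19.1 and 2.21 place the primary comparison at week 8, for PASI and BMI, using a linear mixed model for repeated measures.

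**The concern.** Both analysis-set statements carry the ITT label, and they disagree about the participants for whom the label matters most: those lost early. The number of assessments a person completes is settled after randomisation. A minimum number therefore selects on an event that treatment may influence, which is what section 2.21 says it wants to avoid.

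The lateness rule adds to this. Someone discontinued at week 4 for late attendance may be willing and able to be measured at week 8, yet the article makes no provision for it. The trial would then create missing primary data that it could have collected, and would fall back on one of three incompatible substitutes. The choice among those could be made after the data are seen.

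**Working it through.** **1. The two ITT rules side by side.** Table 1 schedules PASI and BMI at weeks 0, 4 and 8 up to the endpoint. Section 2.15 says assessments during treatment are biweekly. For participants later lost to follow-up:

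| Data before loss | Section 2.21 | 2.18, baseline counts | 2.18, baseline does not count |
|---|---|---|---|
| Baseline only | In | Out | Out |
| Baseline + one later assessment | In | In | Out |
| Baseline + two later assessments | In | In | In |

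The first row conflicts on either reading, and the second on one of them. If both assessments must follow baseline and the Table 1 schedule applies, only weeks 4 and 8 are available, so anyone lost before week 8 is excluded. Biweekly assessments would soften this.

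**2. What the exclusion does to the estimate.**
- Baseline counts: those excluded have no value after baseline. A mixed model on change from baseline gets no outcome from them in any case. The condition then matters only if values are imputed or carried forward.
- Baseline does not count: people with one usable later value are removed, and the mixed model loses information it would otherwise use.

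**3. A participant discontinued for lateness at week 4, with no week-8 measurement.**
- Section 2.8.1: stays in, with the last earlier value standing for week 8.
- Section 2.21, first paragraph: stays in, by imputation or through the mixed model.
- Section 2.21, last sentence: drops out as incomplete, if that sentence governs the primary analysis. It follows text on adverse events and subgroups, so its scope is unclear.
- Section 2.18: drops out if there are fewer than two assessments. An early termination visit might supply one, but at the time of leaving, not at week 8.

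**4. How much loss the plan can absorb.** Inputs from section 2.11: p1 = 0.60, p2 = 0.25, Z values 1.96 and 0.84, dropout 20%.

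n = (1.96 + 0.84)² × [0.60 × 0.40 + 0.25 × 0.75] / 0.35² = 7.84 × 0.4275 / 0.1225 = 27.36, rounded up to 28. Then 28 / 0.80 = 35 per group, 70 in total. The stated figures reproduce.

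Power with m per group, same unpooled variance: Φ(0.35 / √(0.4275/m) − 1.96).

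| Loss | m per group | Power |
|---|---|---|
| 0% | 35 | 88.6% |
| 20% (planned) | 28 | 80.9% |
| 25% (assumed) | 26 | 77.9% |
| 30% (assumed) | 24 | 74.6% |

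These figures use the response-rate comparison on which the trial was sized, not the continuous mixed-model analysis. They show only that the 20% allowance is fully used at the planned loss.

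**The case against.** The best defence is that the article contains several safeguards. Section 2.21 says participants are analysed in the group to which they were randomised. Eligibility (section 2.5) requires PASI or BSA, and BMI, so few or no randomised participants should lack a baseline. Section 2.8.1 keeps withdrawn participants' data, section 2.18 seeks outcomes at an early termination visit, and imputation or mixed models are preferred. Section 2.18 also promises flexible scheduling, and visit windows may be in the full protocol, which is not shown.

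Much of this stands, and it rules out three stronger readings:

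- **A reader might infer that section 2.21 ignores randomisation and admits people never randomised.** It does not: a person without an allocated group cannot be analysed by group. The opening sentence is loosely worded, but in practice it comes close to all randomised. The real exclusion comes from section 2.18.
- **A reader might infer that late attenders are lost from the primary comparison.** That follows only from the two-assessment condition or the complete-case sentence. What discontinuation puts at risk is an observed week-8 value.
- **A reader might try to size the bias**, for example by supposing that 3 of 35 verum participants leave after one session with no change, so that excluding them inflates the verum mean by 35/32, about 9%. The leavers and their outcomes would be invented, and such people might meet the two-assessment condition through a termination visit. Section 2.22 lists local reactions and suture expulsion, and only verum contains suture, so loss that differs by arm is possible. But sham uses the same needles and motions, and no rate is given for either arm.

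The safeguards do not remove the contradiction between sections 2.18 and 2.21. Nor do they supply a week-8 measurement after discontinuation, and they disagree among themselves on what replaces it.

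**Conclusion.** The point holds in a limited form. The two-assessment condition in section 2.18 contradicts section 2.21. The participation rule in sections 2.8 and 2.13 leaves open whether week-8 PASI and BMI are still collected after discontinuation for lateness. If they are not, the missing value would be carried forward, imputed, modelled or dropped, depending on which sentence is followed.

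No size or direction of bias can be derived from the documents. The practical stake is that, on the section 2.11 inputs, power is 80.9% once the planned 20% is lost and falls below 80% with any greater loss. This rests on taking the lateness rule as written, without visit windows that the full protocol may contain. The change should be made, ideally before unblinding, but the point does not by itself invalidate the design.

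**What to change.** 1. Define the primary analysis set once, in section 2.21, as all randomised participants analysed as randomised, and delete the two-assessment condition from section 2.18.
2. State in sections 2.8 and 2.13 that after any discontinuation, including for late attendance, week-8 and later outcomes are still collected unless consent is withdrawn. Record lateness as a visit deviation. This step matters most: deleting the two-assessment condition alone adds no outcome for people with nothing after baseline.
3. Reconcile section 2.8.1 and the two missing-data statements in section 2.21 into one primary rule consistent with the mixed model, and label any other method retained as a sensitivity analysis.

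Whether late attendance should end the procedure itself is for the investigators to reconcile with the flexible scheduling in section 2.18. The change asked for here concerns outcome collection only.

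The cost is a minor amendment with matching analysis-plan wording, and a few extra visits to chase. Reminders and travel support are already in the protocol.
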